### Blinding

The nutritionists and physician that will perform the initial evaluation before randomization, the monthly evaluations and anthropometric profile, and the final evaluation of the health care questionnaires after the end of the patient follow-up will be blinded to the patients’ assignments.

### Statistical methods

The EpiData [53] and Statistical Package for Social Sciences [54] software will be used for data entry and analysis, respectively. For categorical data, we will use Pearson’s χ^2^ or Fisher’s exact test to verify the association between variables in the two groups (omega-3 and placebo). Statistical analysis will be performed by descriptive analysis, with numerical variables expressed as the mean and standard deviation (SD) or median and interquartile range. The Kolmogorov-Smirnov test will be used to test the normality of the sample distribution. The Student t test will be used in cases with a normal distribution to compare means between the two groups. The Wilcoxon test will be used in cases with a non-normal distribution. *P* values <0.05 will indicate a significant association in all of the statistical tests used.

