**Methods/Design:**

This is a parallel, randomized, placebo-controlled, double-blind clinical trial with 40 patients that will be conducted at a reference unit for Chagas disease patients, where the patients will be selected. The study will include patients with chronic chagasic cardiomyopathy who are 18 years of age or older. The exclusion criteria are (a) ongoing diarrheal disease, (b) inflammatory bowel disease, (c) diabetes or other endocrine disease, (d) use of fibrates, niacin, or statins, (e) use of anti-inflammatory drugs, (f) pregnant and lactating women, (g) use of vitamin, mineral, or omega-3 supplementation during the previous 30 days, (h) hospital admission during the study, and (i) other associated cardiomyopathies. The intervention will be treatment with omega-3 PUFAs at a dose of 3 g/day for 8 weeks, compared to placebo (corn oil). The primary endpoints will be the concentrations of inflammatory markers (interleukin (IL)-1, IL-2, IL-4, IL-6, IL-10, tumor necrosis factor (TNF)α, interferon (IFN)γ, and transforming growth factor (TGF)β). Secondary endpoints will be the fasting glucose, lipid, and anthropometric profiles. For statistical analysis, we plan to run either a t test or Wilcoxon test (numerical variables) and Pearson’s χ^2^ or Fisher’s exact test (categorical data), as appropriate.

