### Endpoints

The primary endpoint of this study will be the cytokine profile. IL-1, IL-2, IL-4, IL-6, IL-10, TNFα, IFNγ, and TGFβ will be measured in the serum of patients using specific sandwich enzyme-linked immunosorbent assays. Capture and detection antibodies will be obtained from eBioscience (San Diego, CA, USA). The tests will be conducted according to the manufacturer’s instructions and performed in triplicate.

The first secondary endpoint will be the lipid profile. Total cholesterol, triglycerides, and high-density lipoprotein cholesterol (HDL-c) will be measured with enzymatic colorimetric assays using Siemens reagents on a Siemens Dimension RXL chemistry analyzer (Siemens Healthcare Diagnostics, Tarrytown, NY, USA). Low-density lipoprotein cholesterol (LDL-c) and VLDL-c will be calculated according to the Friedewald equation [44].

Another secondary endpoint of this trial will be anthropometric measures. The anthropometric assessment will consist of body mass index (BMI), waist circumference, tricipital skinfold thickness, and arm circumference [45,46]. BMI will be determined using the standard formula: BMI = weight/height^2^[47].

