### Randomization and concealment

After the screening phase, patients will be randomly assigned to 1 of 2 groups of 20 patients each: intervention group or control group. Assignment to either group will be performed by a computer-generated 1:1 randomization. This assignment will occur within randomly ordered blocks of size 4 or 6. This procedure will be conducted using R project software with package 'blockrand’ [52].

The allocation sequence will be concealed from the researchers, who will enroll and assess participants in sequentially numbered, opaque, sealed, stapled envelopes. To prevent subversion of the allocation sequence, the name and date of birth of the participant will be written on the envelope before the envelope is opened. The information in the envelope will be transferred onto the allocation card inside the envelope. Corresponding envelopes will be opened only after the enrolled participants have completed all baseline assessments and at the time of allocation to the intervention. These procedures will be carried out by a professional without access to the baseline evaluation results. The blister packaging and gel capsules of omega-3 PUFAs and placebo will be identical. They will be identified by the lot number on the package, which will be retained in the pharmacy, and only the blisters will be provided to patients. The pharmacist responsible for distribution and compliance assessment will be the only person who can access this information.

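### A Kolmogorov-Smirnov pre-test on about 20 values per arm chooses between Student t and Wilcoxon for each primary cytokine, so test and effect scale depend on the outcome data and can differ across the eight markers

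*Protocol article*

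**What the plan says.** Statistical methods gives one rule for numerical variables, in three steps. First, "The Kolmogorov-Smirnov test will be used to test the normality of the sample distribution". Second, "The Student t test will be used in cases with a normal distribution to compare means between the two groups". Third, "The Wilcoxon test will be used in cases with a non-normal distribution". Summaries follow the same split, "with numerical variables expressed as the mean and standard deviation (SD) or median and interquartile range". The threshold is common to all tests: "values <0.05 will indicate a significant association in all of the statistical tests used". The Abstract repeats the choice between the two tests.

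No other rule for numerical variables is given, so this one governs the primary endpoint. Under Endpoints, that is a profile of eight markers: "IL-1, IL-2, IL-4, IL-6, IL-10, TNFα, IFNγ, and TGFβ will be measured in the serum of patients". On numbers, Randomization and concealment says "patients will be randomly assigned to 1 of 2 groups of 20 patients each".

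The article does not say which form of the Kolmogorov-Smirnov test is meant (with or without the Lilliefors correction for an estimated mean and SD). Nor does it say which values are tested: each arm or both pooled, week 8 or change. A full analysis plan could supply those details. The two-stage rule itself is stated, and it is the subject of this point.

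**The concern.** A normality test at this sample size is a poor guide to the right analysis. With about 20 values it often misses skewness, and how often depends heavily on which form is run. Making the primary test depend on it has two consequences.

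- The primary analysis of each cytokine is known only after its outcome data have been examined.
- The eight markers can end up on different scales, some as differences in means and others as rank comparisons with medians. No common effect measure then describes the cytokine profile, and results cannot be compared from one marker to the next.

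A smaller matter goes with it. The Student t test in the normal branch assumes equal variances, whereas the two SDs quoted for the sample size differ clearly.

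**Working it through.** **Plan's own figure.** The article reports no operating characteristics for the two-stage rule, so there is nothing to reproduce. Its figures enter only as inputs.

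**Inputs from the article.** 20 patients per arm; threshold 0.05 (taken as two-sided); IFNγ 3,986 ± 738 at baseline and 2,922 ± 1,275 after supplementation (Minimum sample size estimation). From these:
- CV: 738/3,986 = 0.185 and 1,275/2,922 = 0.436.
- Ratio of means: 2,922/3,986 = 0.733, a 27% reduction.
- Variance ratio: (1,275/738)² = 2.98.

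**Assumptions.** Values are lognormal with the same log-SD in both arms, σ = √ln(1 + CV²). CVs of 0.7 and 1.0 extend the range and have no source in the article. Wilcoxon is read as the two-sample rank-sum test, used if either arm fails the normality test at 5%.

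**Pre-test thresholds at n = 20.** The distance needed to reject is 0.294 uncorrected and 0.192 with Lilliefors (simulated).

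**Simulation, 20 vs 20, 60,000 trials per row.** Paired entries are Lilliefors / uncorrected. Power is for the 27% reduction.

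| CV | σ | Either arm rejected | Type I error of the rule | Power of the rule | Power, log t | t and Wilcoxon disagree |
|---|---|---|---|---|---|---|
| 0.185 | 0.184 | 17% / 0.1% | 5.3% / 5.1% | 0.999 / 0.999 | 0.999 | 0.1% |
| 0.436 | 0.417 | 45% / 1.4% | 5.4% / 4.9% | 0.618 / 0.596 | 0.627 | 10.3% |
| 0.7 | 0.631 | 73% / 7% | 5.5% / 4.9% | 0.323 / 0.293 | 0.327 | 11.6% |
| 1.0 | 0.833 | 89% / 20% | 5.2% / 4.9% | 0.205 / 0.188 | 0.211 | 10.7% |

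For CV 0.436 to 1.0, the power loss against the log t test is 0.4 to 0.9 points with Lilliefors and 2.3 to 3.4 points uncorrected. With heavier skew (σ = 1.0) and a larger true shift (0.9 log-SD), the uncorrected rule has power 0.73 against 0.79, a loss of about 6 points.

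The tested data set matters less than the form. With the 40 values pooled at σ = 0.42, rejection is 48% with Lilliefors and 3% uncorrected.

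**Consistency across eight markers.** If markers were independent and each went to Wilcoxon with probability 0.45, the chance that all eight get the same test is 0.45⁸ + 0.55⁸ = 0.002 + 0.008 ≈ 1%. At 0.89 it is 0.89⁸ + 0.11⁸ ≈ 39%. Correlation between markers would change these figures.

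**Equal-variance assumption.** Normal data, equal means, SD 738 in one arm and 1,275 in the other, 400,000 trials; the more variable arm is listed second:
- 20 vs 20: Student 5.2%, Welch 5.0%.
- 20 vs 18: Student 5.8%, Welch 5.0%.
- 20 vs 16: Student 6.6%, Welch 5.1%.
- 16 vs 20: Student 4.0%, Welch 5.0%.

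**The case against.** The strongest reply is that the rule is common and does little damage to the error rates. That stands: in these scenarios its type I error never exceeds about 5.5%, and a log-scale test gains only a few points of power. Four stronger readings are tempting, and the documents do not support them.

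- **The test is picked nearly at random.** This fits only the Lilliefors form at moderate skew (45% at CV 0.44). At CV 1.0 that form picks Wilcoxon in 89% of trials, while the uncorrected form keeps the t test in about 99% of trials at CV 0.44 and 80% at CV 1.0.
- **Skewed markers mostly go to a raw-scale t test.** This holds only for the uncorrected form, and the article does not say that this is the one meant.
- **The cytokines are skewed.** The article does not say so and quotes IFNγ as mean ± SD. Lognormality is my assumption. At the baseline CV of 0.185, a 27% reduction is detected almost always by either test.
- **Student t is seriously anti-conservative here.** A size of about 7.5% needs 20 vs 14, a 30% loss confined to the more variable arm. The article plans 20 vs 20 and gives no loss rate, although Procedures, follow-up, and data collection allows exclusions during follow-up. The two SDs are a before and an after value, not those of concurrent arms, and if the losses fall in the other arm the test is conservative.

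A rank test throughout would also be defensible (power about 0.60 against 0.63 for log t at CV 0.44). The case is for one fixed method; the log scale is one good choice. What the reply does not remove is that the outcome data set the primary test and scale separately for each marker.

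**Conclusion.** The point holds as a should-fix weakness in a rule that the article states. The pre-test fixes the primary analysis only after the data are seen and can spread the eight primary cytokines over two effect scales. For a 27% reduction with CV 0.44 to 1.0, the branch taken could change the significance verdict in about one trial in ten. The average effect on type I error and power is small, so this is a matter of pre-specification and interpretability; it does not show that the trial's conclusions would be unreliable. The equal-variance issue is secondary and matters only if the more variable arm loses more patients. The magnitudes rest on lognormal data, the rank-sum reading of Wilcoxon, and a pre-test in each arm. The data-dependence itself rests on none of these.

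**What to change.** Delete the normality pre-test and name one primary method for all eight cytokines. For example: a linear model of the log week-8 concentration on treatment, adjusted for the log baseline concentration, with heteroscedasticity-robust standard errors (or a Welch t test on log values if unadjusted). Report a geometric mean ratio with 95% CI for every marker, and keep the rank-sum test as a sensitivity analysis for every marker. Baseline cytokines are already measured, so no new data are needed.

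In the scenarios run, a pre-specified log t test kept its size at 4.9% to 5.1%, with power of about 79% for a shift of 0.9 log-SD at every skew tested.

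The cost is wording only, and the change should be made before unblinding. There are two small downsides: results are ratios instead of differences in pg/mL, and the log scale needs a stated rule for any values below the assay's limit.

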## Methods/Design

### Study design

This is a parallel, double-blind, placebo-controlled clinical trial with balanced randomization (1:1).

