### Participants (inclusion and exclusion criteria)

Patients will be recruited from the cardiology ambulatory service at IPEC/Fiocruz, Rio de Janeiro, Brazil, during the period determined for screening until the minimum estimated sample size is reached. All patients had a previous epidemiologic history of Chagas disease confirmed with at least two Chagas serology tests (indirect immunofluorescence and ELISA), and clinical evaluations, electrocardiographic and echocardiographic data obtained recently. Selected patients will be older than 18 years, males and females with CCC at stage B (no heart failure symptoms but with segmental or global left ventricular systolic dysfunction by echocardiogram), stage C (symptomatic heart failure), or stage D (end-stage heart failure), according to the current Brazilian Chagas disease consensus [3]. The following exclusion criteria will be applied: diarrheal disease; inflammatory bowel syndrome; diagnosis of diabetes or other endocrine pathologies; use of fibrates, niacin, or statins; use of anti-inflammatory drugs; pregnant and lactating women; vitamin mineral or omega-3 supplementation during the previous 30 days; hospital admission during the study; and the presence of cardiomyopathies other than CCC.

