### Procedures, follow-up, and data collection

After patients are selected by cardiologists, they will be seen by study nutritionists, who will explain the study procedures to the patients and administer the free and informed consent form. The patients who agree to participate in the study will sign the consent form and undergo the initial assessment.

The following data will be collected and evaluated in the study: sociodemographic data (age, sex, ethnicity/race, education, and domicile), clinical data (functional class and vital signs), alcoholism, smoking, prescription drugs, 3-day food record [48], 24-h recall [49], anthropometric assessment (height, weight, BMI, waist circumference, tricipital skinfold thickness, and arm circumference), lipid profile (total cholesterol, triglycerides, HDL-c, LDL-c, and VLDL-c), and cytokines (IL-1, IL-2, IL-4, IL-6, IL-10, TNFα, IFNγ, and TGFβ). Clinical, nutritional, and anthropometric assessments will take place immediately before starting the intervention and after 4 and 8 weeks during the study; lipid profile and cytokines will be evaluated before the intervention and at the end of 8 weeks. Each patient will be followed for 8 weeks.

Compliance with study treatment will be assessed by the 3-day treatment recall and the number of omega-3/placebo capsules returned. At every visit, the patients will be asked about the number of doses of the prescribed treatment that they did not take during the previous 3 days, and the ratio between the number of doses taken and the number prescribed will be calculated. The capsules will be dispensed at the beginning of the study and after 4 weeks, and the returned capsules will be verified at weeks 4 and 8.

The dietary omega-3 PUFA intake will be followed-up during the study (first visit and weeks 4 and 8) by analyzing the 24-h recall and 3-day food record, which are considered indirect methods of analyzing the diet, current dietary standards of a certain population, and their development over time [50].

Patients may be excluded from the study in case of complications during follow-up, such as significant changes in intestinal transit, use of anti-inflammatory drugs, and hospital admissions. Other complications will be assessed by the study team. All endpoints will be collected at time 0 and 8 weeks after omega-3/placebo supplementation starts.

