### Minimum sample size estimation

The minimum estimated sample size is 40 patients according to previous data, considering a prevalence of 60% of inadequate PUFA intake [55]. The following parameters were considered: baseline IFNγ = 3,986 ± 738 pg/mL, IFNγ after *n*-3 PUFA supplementation = 2,922 ± 1,275 pg/mL [56], power = 0.8, and α = 5%. We used the R project software with package 'Epicalc’ version 1.02 [57] to obtain this estimate.

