A clinical trial evaluated 3-month omega-3 PUFA supplementation in patients with heart failure. Patients were divided into three groups: placebo, 1 g/day omega-3 PUFAs, and 4 g/day omega-3 PUFAs. Only the 4 g/day group had an improvement in ventricular function with an increase in the ejection fraction and endothelial function and a reduction in IL-6 [36]. We will use 3 g/day omega-3 PUFAs in our study based on recent results suggesting higher efficacy when compared to the usual 1 g dose, in addition to the fact that 3 g/day is considered safe by the FDA [51]. According to a recent American College of Cardiology and American Heart Association (ACC/AHA) Heart Failure Guideline, omega-3 supplementation is reasonable to use as adjunctive therapy in heart failure patients (Class of Recommendation IIa, Level of Evidence B ) [62].

The worse prognosis and progression of CCC are related to increased immune response with the production of proinflammatory cytokines and the inhibition of anti-inflammatory cytokines, which also occur in other cardiomyopathies [63,64]. In Chagas disease, heart tissue is an important target of *T. cruzi* infection, and substantial amounts of proinflammatory cytokines, chemokines, and enzymes, including inducible nitric oxide synthase and metalloproteinases, are produced, resulting in inflammation and cardiac remodeling in response to parasite infection [65]. Higher levels of IFNγ and TNFα are associated with lower levels of IL-4 and IL-10, in both cardiac and more severe forms of Chagas disease, and high levels of IL-10 or moderate levels of IFNγ are associated with the indeterminate form [15,66]. Omega-3 and omega-6 PUFA intake may lead to an increase in IL-10 production, as shown in an experimental study in Wistar rats supplemented with ethyl-eicosapentaenoic acid and ethyl-γ-linolenic acid compared to a group supplemented with palm oil [67]. Thus, omega-3 PUFA supplementation in CCC patients may lead to increased IL-4 and IL-10, reducing the inflammatory effect on heart tissue.

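### Every endpoint has a baseline value, but the stated two-group test makes no adjustment for it; an analysis adjusted for baseline would gain precision from data already collected

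*Protocol article*

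**What the plan says.** Statistical methods in the protocol article sets the comparison for numerical variables: "The Student t test will be used in cases with a normal distribution to compare means between the two groups". The Wilcoxon test replaces it when the distribution is not normal, and the abstract names the same pair of tests. No regression model or covariate appears anywhere, and the text does not say whether the tests are applied to week-8 values or to changes from baseline.

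Procedures, follow-up, and data collection states that "lipid profile and cytokines will be evaluated before the intervention and at the end of 8 weeks", and closes by saying that all endpoints are collected at time 0 and at 8 weeks. Randomization and concealment states that "patients will be randomly assigned to 1 of 2 groups of 20 patients each", in blocks of 4 or 6. Envelopes are opened only after baseline assessments are complete, so the baseline values are true pre-randomisation covariates.

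**The concern.** With 20 patients per arm, precision is scarce. A patient's cytokine or lipid value at entry will usually predict the value at week 8, and the named tests cannot take a covariate.

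- If they are applied to week-8 values, the baseline measurement is ignored.
- If they are applied to change scores, baseline is used, but with a fixed coefficient of 1 in place of the one that the data support.

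In a small trial, part of any chance baseline difference between arms also carries into the week-8 contrast, and no described step of the analysis removes it. At stake is power for effects smaller than the design effect, and how well the estimate can be read if the arms happen to differ at entry.

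**Working it through.** **The plan's own figure.** Minimum sample size estimation states: "The minimum estimated sample size is 40 patients according to previous data". The inputs are "baseline IFNγ = 3,986 ± 738 pg/mL", 2,922 ± 1,275 pg/mL after supplementation, power 0.8 and α 5% (two-sided assumed).

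- Difference: 3,986 − 2,922 = 1,064.
- Root-mean-square SD: √[(738² + 1,275²)/2] = √[(544,644 + 1,625,625)/2] = 1,041.7.
- Standardised effect: 1,064/1,041.7 = 1.02.
- n per arm: (1.960 + 0.842)² × (738² + 1,275²)/1,064² = 15.05, so 16 per arm and 32 in total.

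The stated 40 is not reproduced. It exceeds 32, so this does not affect the present point. The exact t-test power with 20 per arm at 1.02 SD is 0.88.

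**Variance relative to the week-8 comparison** (equal SDs at both times and in both arms):

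- Week-8 value: 1
- Change score: 2(1 − ρ)
- ANCOVA: 1 − ρ²

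The difference 2(1 − ρ) − (1 − ρ²) equals (1 − ρ)², which is positive for any ρ below 1. So ANCOVA beats the change score throughout. The change score is worse than ignoring baseline when 2(1 − ρ) > 1, that is, when ρ < 0.5.

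**Equivalent patients per arm** for a week-8 comparison, 20/(1 − ρ²):

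- ρ = 0.3: 20/0.91 = 22.0
- ρ = 0.5: 20/0.75 = 26.7
- ρ = 0.7: 20/0.51 = 39.2

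**Power** (noncentral t, 20 per arm, two-sided 5%). The ρ values and the 0.7 SD effect are assumptions; 1.02 SD comes from the protocol.

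| Effect | Analysis | ρ = 0.3 | ρ = 0.5 | ρ = 0.7 |
|---|---|---|---|---|
| 1.02 SD | Week-8 t test | 0.88 | 0.88 | 0.88 |
| 1.02 SD | Change score | 0.76 | 0.88 | 0.98 |
| 1.02 SD | ANCOVA | 0.91 | 0.95 | 0.99 |
| 0.7 SD | Week-8 t test | 0.58 | 0.58 | 0.58 |
| 0.7 SD | Change score | 0.45 | 0.58 | 0.80 |
| 0.7 SD | ANCOVA | 0.62 | 0.70 | 0.86 |

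A simulation of 20,000 trials per setting, which also estimates the slope, gave ANCOVA power of 0.90, 0.95 and 0.99 at 1.02 SD. Type I error lay between 4.6% and 5.2% for all three analyses, with ρ from 0 to 0.7.

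**Chance imbalance.** The difference in baseline means has standard deviation √(2/20) = 0.316 SD. P(|difference| > 0.5 SD) = 2[1 − Φ(0.5/0.316)] = 0.114 for a given marker. The expected carry-over into the week-8 contrast is ρ times the imbalance. A 0.5 SD imbalance therefore carries 0.15, 0.25 or 0.35 SD at ρ = 0.3, 0.5 or 0.7.

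**The case against.** The strongest defence is that nothing stated is wrong. Both tests are valid under randomisation, and their standard errors already allow for chance imbalance on average. The gain rests on a correlation that the documents do not give: it is modest at ρ = 0.3, and at ρ = 0 about one power point is lost (0.87 against 0.88 in the simulation at 1.02 SD). At the protocol's own effect, power is already 0.88. If change scores are intended and ρ is 0.7, the gap at 0.7 SD is 0.80 against 0.86, not 0.58 against 0.86. All of this stands, and it makes the point one of efficiency.

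It might also be said that covariates belong in an analysis plan that is not shown. That carries less weight here, because the article does not leave the method open: it names tests that cannot take a covariate.

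A reader might infer three stronger things that the documents do not support.

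- **That the planned test is biased or inflates false positives.** It does neither; type I error stays near 5%.
- **That a baseline imbalance passes in full into the week-8 result.** Only ρ times the imbalance is expected to.
- **That the article shows cytokine levels to differ by heart-failure stage, so that stage must be adjusted for.** The Discussion describes a cytokine pattern "in both cardiac and more severe forms of Chagas disease" and sets it against the indeterminate form. The trial enrols only cardiomyopathy at stages B to D, so that sentence says nothing about B against C or D.

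**Conclusion.** The point holds as an improvement that uses existing data, not as an error that invalidates the trial. The stated analysis is valid but inefficient. On either reading of what is compared, adjusting for baseline does better for any ρ strictly between 0 and 1, apart from the small cost of estimating one slope, which matters only when ρ is near 0.

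The size depends on assumption. Over ρ of 0.3 to 0.7, power against a week-8 t test rises by 0.03 to 0.11 at the protocol's effect and by 0.04 to 0.28 at 0.7 SD. Smaller effects are plausible: the Background cites an 8-week fish-oil study in healthy adults with no change in IFNγ, TNFα or IL-10.

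The figures assume normal data and equal SDs. The protocol's own two SDs differ (738 and 1,275), so the figures show the order of the gain rather than forecast it, and they do not transfer automatically to a log scale.

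**What to change.** By a dated amendment before unblinding:

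1. Make the primary analysis of each cytokine a linear model of the week-8 value on arm and baseline value. Use the log scale if values are skewed, with a stated rule for undetectable values. Report the adjusted effect with a 95% CI.
2. Use the same form for lipids and anthropometry.
3. Keep the two-sample test as a sensitivity analysis, and state whether it compares week-8 values or changes.
4. Treat a disease-stage covariate as optional.

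The cost is the amendment itself, since Trial status says that recruitment is under way, and one residual degree of freedom. No extra measurement is needed, and the named statistical package fits this model.

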**Discussion:**

Evidence suggests that the anti-inflammatory action of omega-3 PUFAs may have beneficial effects on chronic chagasic cardiomyopathy, as shown for other cardiomyopathies, due to improved control of the inflammatory response. At the end of the study, we predict that patients will have lower inflammatory markers and an improved metabolic and anthropometric profile.

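### Eight cytokines are all primary and each is judged at unadjusted P<0.05, with no lead marker or success rule, although the trial was sized on IFNγ alone

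*Protocol article*

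**What the plan says.** - **Primary endpoint.** The abstract (Methods/Design) uses the plural: "The primary endpoints will be the concentrations of inflammatory markers", followed by eight names. The Endpoints section uses the singular: "The primary endpoint of this study will be the cytokine profile". It then lists the same eight: "IL-1, IL-2, IL-4, IL-6, IL-10, TNFα, IFNγ, and TGFβ will be measured in the serum of patients". Neither place defines a score that combines them, ranks them, or says which must change.
- **Tests.** Statistical methods describes separate two-group comparisons: "The Student t test will be used in cases with a normal distribution to compare means between the two groups", with the Wilcoxon test where the distribution is not normal.
- **Threshold.** The same section closes by saying that P "values <0.05 will indicate a significant association in all of the statistical tests used". No adjustment is mentioned.
- **Sizing.** Minimum sample size estimation works from one outcome: "The following parameters were considered: baseline IFNγ = 3,986 ± 738 pg/mL, IFNγ after" supplementation 2,922 ± 1,275 pg/mL, with power 0.8 and α 5%. A 60% prevalence of inadequate PUFA intake is also cited, but it is not an outcome.
- **Expected direction.** The abstract's Discussion says "we predict that patients will have lower inflammatory markers". The main Discussion says that supplementation "may lead to increased IL-4 and IL-10".

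**The concern.** A 5% threshold protects a conclusion only if that conclusion rests on one test, or if the tests behind it are controlled together. Here eight tests bear on the primary question, each has its own 5%, and nothing says how the eight results become one answer. A report that found one cytokine below 0.05 and seven above could call this a significant result on a primary endpoint without departing from the text.

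What is at stake is the main conclusion of a 40-patient trial. An inert supplement would have a much larger chance than 5% of yielding at least one significant primary cytokine. The planned power, meanwhile, applies to only one of the eight.

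**Working it through.** **Inputs from the protocol article.** Eight primary cytokines (abstract; Endpoints). A threshold of 0.05 per test (Statistical methods). Twenty patients per arm (Randomization and concealment). IFNγ 3,986 (SD 738) and 2,922 (SD 1,275) pg/mL, α 5%, power 0.8 (Minimum sample size estimation).

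**Assumptions, not in the document.** Two-sided tests; a common pairwise correlation between cytokines, varied from 0 to 0.9; the before/after IFNγ figures taken as a between-arm difference; no dropout.

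**1. The plan's own figure.** The difference is 3,986 − 2,922 = 1,064. For two independent means:

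n per arm = (738² + 1,275²)(1.960 + 0.842)² / 1,064² = 2,170,269 × 7.849 / 1,132,096 = 15.05, so 16 per arm and 32 in total (34 by the t distribution).

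The stated 40 does not follow from these inputs at power 0.8. That is a separate matter and does not affect the multiplicity point. What matters here is that only IFNγ enters the calculation.

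**2. Family-wise error, independent tests, no true effect on any cytokine.**

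1 − (1 − 0.05)⁸ = 1 − 0.95⁸ = 0.337.

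**3. Family-wise error, correlated tests.** Simulation of eight equally correlated two-sided tests at 0.05:

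| Common correlation | Normal tests (1,000,000 draws) | t tests, 20 per arm (100,000 trials) |
|---|---|---|
| 0 | 33.7% | 33.7% |
| 0.3 | 29.9% | 30.0% |
| 0.5 | 25.1% | 25.3% |
| 0.7 | 19.0% | 19.5% |
| 0.8 | 15.8% | not run |
| 0.9 | 11.9% | not run |

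Even at 0.9 the figure is more than twice 5%.

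**4. Price of adjusting across all eight.** The Bonferroni level is 0.05/8 = 0.00625, and the family-wise error for independent tests is then 1 − (1 − 0.00625)⁸ = 4.9%. For IFNγ at 20 per arm, the standard error is √(2,170,269/20) = 329.4, and the standardised difference is 1,064/329.4 = 3.23.

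| Method | Power at 0.05 | Power at 0.00625 |
|---|---|---|
| Normal approximation | 0.90 | 0.69 |
| Student t | 0.88 | 0.63 |
| Welch t | 0.88 | 0.62 |

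Power of 0.80 at 0.00625 would need 25 per arm (normal) or 27 per arm (t). Holm is never less powerful than Bonferroni, so 0.62-0.63 is its worst case.

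**5. Why the secondary cytokines need a gate.** If IFNγ is tested at 0.05 and the other seven by Holm at 0.05 regardless of the IFNγ result, the error across all eight is 1 − 0.95 × 0.95 = 9.75% when the two parts are independent, and at most 10%. Testing the seven only after a significant IFNγ keeps it at 5%.

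**The case against.** **The document does not say that one significant cytokine makes the trial positive.** This is correct. Statistical methods says only that a P value below 0.05 marks a significant association. A reader might infer that any one of eight is declared sufficient, but the text does not support that. The 33.7% describes one permitted reading, in which no cytokine truly responds. The criticism that stands is that the text sets a per-test threshold and no rule to exclude that reading.

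**The 5% is a sizing α, not a promised family-wise rate.** This is also fair. The document does not claim to hold 5% across the eight cytokines, so the error is not a breach of a stated guarantee. The fault is that sizing and endpoint definition address different questions.

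**An analysis plan may settle it.** An article may leave detail to a plan that is not shown. Here, however, the article itself fixes the threshold for all tests and gives all eight markers primary status. A plan that adjusted or chose one marker would depart from this text.

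**The range depends on correlations nobody has stated.** This is accepted. A reader might take 19-30% as bounds, but they are only the values at correlations of 0.7 and 0.3.

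**The direction of effect.** A reader might infer that the protocol contradicts itself, because IL-4 and IL-10 sit among markers predicted to fall and are elsewhere expected to rise. The document does not support so strong a reading. The objective at the end of the Background separates proinflammatory from anti-inflammatory cytokines, and the Discussion predicts a fall only for the former. The abstract is loosely worded, and nothing more.

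**IFNγ is not the only candidate.** The Background cites an 8-week study in healthy adults in which IL-6 fell but IFNγ did not change, and the heart-failure meta-analysis in the Discussion concerns TNFα, IL-1 and IL-6. The sponsor may prefer another single marker, but would then have to redo the sizing.

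**Conclusion.** The point holds. As written, the primary question is answered by eight unadjusted tests with no lead marker, hierarchy or success rule, while the sample size supports one of them. If any one significant result is treated as a positive primary finding and there is no true effect, the false-positive chance is 33.7% under independence and falls to about 12% at a common correlation of 0.9. No correlation in the range examined brings it near 5%. These figures rest on two-sided tests, equal correlations and the any-one-significant reading. None of the three is stated in the document, so they show the size of the exposure and are not the trial's known error rate.

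This should be corrected before the data are unblinded, because it determines what the trial can conclude. The wording about direction is minor and adds no weight.

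**What to change.** By a dated amendment before unblinding:

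1. Name week-8 IFNγ, the only cytokine used for sizing, as the single primary endpoint, tested at two-sided 0.05.
2. Make the other seven cytokines secondary. Test them with Holm only if IFNγ is significant; otherwise report them as exploratory.
3. Report P values for the lipid and anthropometric endpoints as nominal, and replace the blanket 0.05 sentence accordingly.
4. State in the abstract that the predicted fall concerns the proinflammatory cytokines, since IL-4 and IL-10 are expected to rise.

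If the sponsor wants to keep all eight primary, apply Holm across the eight, state what counts as success, and restate the power at 20 per arm on the figures above.

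**Cost.** No extra patients, samples or assays under the single-primary option. A lone nominal P<0.05 on another cytokine would no longer count as a primary success, and the stated objective becomes narrower. Trial status says that recruitment is under way, so this is a change of primary endpoint during the trial: the registry entry and the ethics record must be updated as well as the text.
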